### Blinding

2.8

The nature of the interventional procedures anticipated for this study does not permit the activation of a blindness mechanism in the subjects involved. The study will be carried out as a single-blind study. In particular, participants will be contacted by telephone by the evaluator, independently of the coordinator (and possibly the clinician). Participants will be asked not to disclose to the evaluator which therapeutic interventions they are receiving.

### Interventions

2.9

#### Control: Treatment as Usual (TAU)

2.9.1

Treatment as usual (TAU) path, following the guidelines of the Italian Association of Medical Oncology (AIOM-SIPO: https://www.aiom.it), is an active comparator and includes an initial psychiatric visit aimed at assessing the presence of psychopathological conditions that may necessitate pharmacological therapy and subsequent psychiatric follow-up. The treatment will also involve psychological counselling (bi-monthly sessions) for 12 consecutive weeks. The duration of each session will be 50 minutes.

#### Experimental 1: Virtual Reality-based Cognitive Remediation (VR-COG) + Treatment as Usual (TAU)

2.9.2

 The "VR-COG" experimental protocol integrates sailing virtual environments within the CEREBRUM software platform (Idego-Promind, srl, Rome, Italy). It is based on the virtual reality software CEREBRUM (Idego-Promind, srl, Rome, Italy). The virtual scenarios dedicated to the sport of sailing offer four cognitive training exercises, each with three progressively challenging levels of difficulty, designed to train different cognitive functions (*i.e.*, executive functions, motor ability, language). The different degrees of difficulty are designed to adapt to the user's functional diagnosis. Each session, after an initial part of welcome, psychoeducation, and orientation to the instrument, involves alternating virtual reality exercises, positive and corrective feedback, and suggestions of practical homework that the individual should try to do during the day [16-22]. The frequency is 24 sessions, 2 times a week, for 12 consecutive weeks. The duration of each session is 50 minutes.

#### Experimental 2: Repetitive Transcranial Magnetic Stimulation (rTMS) + Treatment as Usual (TAU)

2.9.3

The rTMS group will receive active rTMS using the MagVenture MagPro X100 System (MagVenture A/S, Denmark) equipped with a MagVenture Cool-B65 A/P double-faced coil and a neuronavigation system (Localite GmbH, Sankt Augustin, Germany). Active rTMS stimulation will be delivered at 50% of the resting motor threshold (rMT). Personalized targets created for each individual will be located at various cortical depths. For safety reasons, the stimulation intensity will never exceed 120% of the rTMS [44, 45]. The frequency will be 24 sessions, 2 times a week, for 12 consecutive weeks of rTMS with the intermittent theta burst stimulation (iTBS) protocol on the left dorsolateral prefrontal cortex (DLPFC). The daily sessions will consist of 3 consecutive sessions of 600 pulses, with each session comprising triplets of pulses at a frequency of 50 Hz, repeated every 200 ms (5 Hz bursts).

#### Data Management and Security

2.9.4

The main goal of the data management process is to guarantee the timely delivery of high-quality data in order to meet the requirements of appropriate statistical analysis and good clinical practice (GCP) standards [46]. It includes all phases of data management, such as data collection, processing, and application. All clinical data will be collected in a comprehensive longitudinal database to facilitate research procedures. Patient information will be recorded *via* IT (information technology) support (REDCap 8.10.18) with reserved and controlled access [47]. Each participant will be assigned a unique identification number at the start of the study. As well, EDC (electronic data capture) will be developed. This record will be used to design, build, and implement a database for data collection, manage data quality, create automated queries for study monitoring, harmonize data provided by different sources, and export the collected data in formats useful for statistical processing. The study will be conducted following the Declaration of Helsinki [48] and the requirements of all applicable local and international standards, according to data protection laws. Written informed consent from all patients will be obtained before data collection.

#### Methods to Handle Missing Data

2.9.5

Special efforts will be made to minimize missing data rates and collect data related to the outcomes for participants withdrawing early from the study. This will include proposing evaluations *via* telemedicine platforms or non-video-recorded video calls, or setting up new check-ups at 3, 6, and 9 months.

#### Adverse Event Reporting

2.9.6

The clinicians in charge of TAU at each appointment will collect, report, evaluate, and manage adverse events or other unexpected effects of the interventions being studied or related to the trial's implementation. Each adverse event will be reported, including details about the type of adverse event, its beginning and end, severity, whether or not it could have been expected, its outcome, and whether or not it was related to the study.

#### Oversight and Monitoring

2.9.7

The dissemination committee will be formed with representatives from both units. The committee will be chaired by the principal investigator from unit 1, who will be responsible for the final decisions. An interim analysis is planned at 70% of the recruitment. Monthly intra- and inter-centre meetings will be scheduled to monitor the progress of recruitment, the safety of interventions, and data collection. The meetings will take place independently of the sponsor.

### Ethical Issue

2.10

According to the Declaration of Helsinki's guidelines [48], each study participant will provide their signed informed consent. The processing of personal data used in the healthcare sector will comply with the legislation under Regulation (EU) 2016/679 (General Data Protection Regulation - GDPR). The clinicians responsible for the TAU at units 1 and 2 will collect written informed consent.

The study protocol has been approved by the ethics committee “Area Vasta Emilia Centro della Regione Emilia-Romagna (CE-AVEC)”, Italy (199/2023/Disp/ AUSLFe, 04/04/2023), and by the ethics committee “Azienda Ospedaliero-Universitaria di Cagliari”, Italy (Prot. NP/2023/1566, 06/04/2023).

### Statistical Analysis

2.11

The baseline data will be summarised as percentage (absolute numbers) for qualitative variables and median (1^st^ and 3^rd^ quartiles) for continuous variables. The group sequential Bayesian design [49] will be used to analyze the study's primary endpoints. Additionally, the first interim analysis will be carried out when 70% of enrolment is reached. The pattern chosen for the evaluation of the risk ratios of the primary endpoint will be defined by a beta-binomial model [50]. Apart from that, a SHELF (Sheffield Elicitation Framework) elicitation paradigm [51] will be used to define the prior probability of remission in the three intervention groups. The elicitation procedure will be carried out using R Shelf software [52]. Non-informative priors will still be used for sensitivity analyses. Upon reaching the interim, the probability that the posterior RR (relative risk) estimates, for the TAU *versus* rTMS or TAU *versus* VR-COG comparison, imply a value greater than 1 and surpass an efficacy boundary established in the interim, will be calculated. If at least one posterior probability for comparison using informative and non-informative priors exceeds the interim boundaries, then the trial will end due to efficacy; otherwise, the trial will continue until the end of the study. If the trial advances, the posterior probabilities for the RRs, with 95% confidence intervals, will be calculated. The intervention will be considered effective if the posterior probability that the RR exceeds 1 is higher than the ultimate effectiveness boundary. Secondary analyses will be performed using generalized Bayesian models by taking into account the interventions as a covariate and reporting 95% posterior confidence intervals. The convergence of the models will be evaluated using trace plots and Gelman statistics. The data will be analysed with an intention-to-treat approach and imputation of missing data according to a Last Observation Carried Forward (LOCF) protocol [53].

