### Outcomes

2.3

The following outcome measures will be established for each participant based on clinical relevance, Cochrane Collaboration indications, and cost-effectiveness studies.

The primary outcomes will include depressive symptoms and the study’s feasibility indicators (acceptability, tolerability, side effects, or secondary effects due to the use of technological devices).

The secondary outcomes will comprise quality of life, cognitive functions (immediate memory, working memory, phonemic verbal fluency, delayed memory, psychomotor speed, executive function, selective attention), and other depression-related conditions (demoralization, embitter-ment reactions to negative life events, psychological distress, insomnia, social and biological rhythms dysregulation, disability level, and alexithymia).

The tertiary outcome will include the cost-effectiveness of the nonpharmacological interventions (VR-COG, rTMS) in addition to TAU compared to TAU alone.

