### Evaluation Tools and Evaluation Timeline

2.4

To assess the primary outcomes, the tools and evaluation procedures that will be used are as follows:

Hamilton Depression Rating Scale, comprising 17 items (HAM-D-17) [24], is a clinician-administered tool widely used to assess the severity of depressive symptoms, which evaluates mood, guilt, suicide ideation, insomnia, and somatic symptoms over the preceding week. Each item is rated on a 3- or 5-point scale, with higher scores indicating greater depression severity. Its reliability and validity have been extensively established. The scale will be administered according to the following timeline: T0 (0 months-baseline), T1 (3 months-post-intervention), T2 (3 months after T1), and T3 (6 months after T1).Drop-out rates, the proportion of recruited participants among those considered eligible, and secondary or side effects due to virtual reality or repetitive transcranial stimulation will be the measures employed to assess the feasibility of the study. These will be estimated according to the following timeline: T0 (0 months-baseline), T1 (3 months-post-intervention), T2 (3 months after T1), and T3 (6 months after T1). Side and secondary effects will be assessed through the Simulator Sickness Questionnaire [25], a self-report questionnaire including 16 items that evaluate the frequency of unwanted effects due to virtual reality technologies, such as nausea, dizziness, headaches, eye strain, *etc.* The TMSens_Q questionnaire [26] will be used to evaluate various unintended sensations and adverse effects, ranging from mild side effects to serious adverse events related to the use of rTMS. The questionnaire will be administered according to the following timeline: T0 (0 months-baseline) and T1 (3 months-post-intervention). Figure **1** provides a summary of the timeline.

To assess the secondary outcomes, the following tools and evaluation procedures will be employed:

EuroQol (EQ)-5D is a self-report questionnaire to assess health-related quality of life [27]. It encompasses two parts: a descriptive one and a visual analogue scale (VAS). The descriptive part includes five dimensions, including mobility, self-care, usual activities, pain/

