### Randomization

2.6

As shown in Fig. (**2**), the randomization will be conducted at units 1 and 2 after baseline assessment. Randomization will be computer-based and concealed. The people who will conduct the randomization procedure will be blind to the participants’ identities and status and will not receive any information on the participants. Randomization will be performed by blocks of randomized permutations to experimental and control treatments at a 1:1:1 (unit 1) and 1:1 rate (unit 2). Codes will be masked.

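### As written, LOCF covers the two side-effect questionnaires, so a participant with no T1 form would normally be given a pre-exposure score as if it were post-exposure

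*Protocol article*

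**What the plan says.** The missing-data rule closes section 2.11 (Statistical Analysis), after both the primary and the secondary analyses: "The data will be analysed with an intention-to-treat approach and imputation of missing data according to a Last Observation Carried Forward (LOCF) protocol". No outcome is set apart from it.

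Section 2.3 (Outcomes) places depressive symptoms and the study's "feasibility indicators (acceptability, tolerability, side effects, or secondary effects due to the use of technological devices") among the primary outcomes. Section 2.4 repeats this for the measures: "secondary or side effects due to virtual reality or repetitive transcranial stimulation will be the measures employed to assess the feasibility of the study". The instruments named there are the Simulator Sickness Questionnaire for VR and TMSens_Q for rTMS. The schedule that follows TMSens_Q reads "The questionnaire will be administered according to the following timeline: T0 (0 months-baseline) and T1 (3 months-post-intervention").

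On timing, section 2.6 says that "the randomization will be conducted at units 1 and 2 after baseline assessment". Exposure then runs to 24 sessions in each device arm: "The frequency is 24 sessions, 2 times a week, for 12 consecutive weeks" for VR-COG (section 2.9.2) and "The frequency will be 24 sessions, 2 times a week, for 12 consecutive weeks of rTMS" (section 2.9.3).

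Section 2.9.5 offers people who withdraw early either remote evaluations, with no stated time, or "setting up new check-ups at 3, 6, and 9 months". Section 2.9.6 has the clinicians in charge of TAU record adverse events at each appointment, including whether each was related to the study.

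**The concern.** LOCF needs an earlier value that bears on the later one. For a depression score, baseline is at least a measurement of the same condition. For a device side-effect questionnaire, baseline can show only background symptoms, such as nausea or headache from other causes. It carries no information about VR or rTMS. Placing it in the T1 column labels a pre-exposure score as post-exposure, and it also hides that the form is missing.

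At stake is the tolerability summary. Section 4 (Study Limitations) describes the trial as a pilot meant to guide later, adequately powered trials, so tolerability is one of its main products. The arms are small, and a few filled-in forms could make up a visible share of the summary.

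**Working it through.** The plan gives no figure to reproduce on this point. The check is first one of timing and then of algebra.

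**Timing**

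1. Scope: section 2.11 applies LOCF to the data without exception, and side effects are among the primary feasibility indicators (sections 2.3 and 2.4).
2. T0 comes before randomization (section 2.6), and so before every device session.
3. No side-effect form is scheduled between T0 and T1. The schedule sentence in section 2.4 is singular and may cover TMSens_Q only; an earlier sentence there gives T0 to T3 for side effects in general. On either reading T0 is the only scheduled form before T1. On the longer reading, T0 would also fill T2 and T3 for someone who never returned a later form.
4. The extra check-ups in section 2.9.5 start at 3 months. The remote evaluations have no stated time, so one of them could capture a post-exposure form, but none is scheduled to do so.

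So T0 is the only *scheduled* value that LOCF can carry to T1.

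**Effect on the T1 mean**

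Let d be the share of the arm with no T1 form, Y1c the completers' mean at T1, and Y0d and Y1d the non-completers' means at T0 and (true) T1.

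- LOCF mean = (1 - d) × Y1c + d × Y0d
- True mean = (1 - d) × Y1c + d × Y1d
- Difference = -d × (Y1d - Y0d) = -d × c, where c is the non-completers' true mean change

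The mean change from T0 differs by the same amount. If c > 0, LOCF understates side effects; if c = 0, there is no bias; if c < 0, LOCF counts against the device.

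**Illustration (d and k are assumptions; the documents give neither)**

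Arm sizes follow from the abstract: VR-COG 20 + 20 = 40, rTMS 20. With d at 10%, 20% or 30%, the number carrying a pre-exposure score would be 4, 8 or 12 of 40 in VR-COG and 2, 4 or 6 of 20 in rTMS.

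Write m for the completers' mean change and c = k × m. Then, relative to the true mean change:

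- LOCF: (1 - d) / ((1 - d) + d × k)
- Observed forms only: 1 / ((1 - d) + d × k)

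| d | LOCF, k = 0 | LOCF, k = 0.5 | LOCF, k = 1 | Observed, k = 0 | Observed, k = 0.5 | Observed, k = 1 |
|---|---|---|---|---|---|---|
| 10% | 100% | 0.90/0.95 = 95% | 90% | 1/0.90 = 111% | 1/0.95 = 105% | 100% |
| 20% | 100% | 0.80/0.90 = 89% | 80% | 1/0.80 = 125% | 1/0.90 = 111% | 100% |
| 30% | 100% | 0.70/0.85 = 82% | 70% | 1/0.70 = 143% | 1/0.85 = 118% | 100% |

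**Break-even.** The error of LOCF is d × |k| × |m|, and that of observed-only is d × |1 - k| × |m|. Observed-only is closer to the truth when |1 - k| < |k|, that is, when k > 0.5, whatever d is. Observed scores should therefore not stand alone either.

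**The case against.** The strongest reply is that the LOCF sentence ends a paragraph about remission risk ratios and secondary models. The article describes no analysis of the two questionnaires, and an unseen analysis plan could confine LOCF to efficacy outcomes. That is possible. But the article states a general rule with no exemption, so the point concerns a rule that is fixed too broadly, not a detail left out. It is limited to the imputed T1 value and any summary that uses it.

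A reader might infer three stronger things that the documents do not support:

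- *That LOCF will make the devices look better tolerated.* The sign depends on what happened to people without a form. Section 3.1 expects mild and transient effects. For someone who stopped early, these may have gone by 3 months, which puts k near 0. LOCF would then be about right, and observed-only scores would overstate. This stands as a limit on size and sign. It does not rescue the rule, because the agreement would come from an assumption about absent people and not from a measurement.
- *That a pre-exposure score is the only value that could be carried.* A remote evaluation under section 2.9.5 might capture a form after withdrawal. It is neither promised nor excluded.
- *That the tolerability signal is lost or the efficacy conclusion is affected.* Dropout rates (section 2.4), adverse-event reports (section 2.9.6) and monthly safety meetings (section 2.9.7) keep part of the signal. No decision rule uses these scores, and the efficacy decisions rest on remission, which this point does not touch.

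**Conclusion.** The point holds in a limited form. Read as written, the LOCF rule reaches both side-effect questionnaires. A participant with no T1 form, and no form captured at an unscheduled evaluation, is assigned a pre-exposure score that is counted as observed. The bias in the T1 mean is -d × c; neither term can be found from the documents, and it may be small or of either sign. Over the assumed ranges (d from 10% to 30%, k from 0 to 1), the LOCF mean change lies between 70% and 100% of the true one. This is a cheap improvement to the reporting of tolerability, not a threat to the trial's efficacy conclusions.

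**What to change.** Add to section 2.11 that LOCF does not apply to the Simulator Sickness Questionnaire and TMSens_Q. Report observed post-exposure scores among participants who started the device, with the number missing.

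Because observed scores alone can also mislead, report beside them, by arm:

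- the dropout rate already planned in section 2.4;
- the adverse events judged related under section 2.9.6, with a note that relatedness is recorded to the study and not to the device;
- stops due to side effects, but only if the reason for stopping is recorded, which the article does not promise.

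The cost is a short addition to the analysis text, with no new visit. The downside is that the score summary rests on fewer participants and that tolerability may look less favourable.

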### Participants and Recruitment

2.2

The target population for this study will be subjects with oncological diseases and moderate depression. Inclusion criteria will be as follows: patients aged 18 years and older of both genders; diagnosis of oncological disease in the last 5 years; depression without psychotic symptoms according to Hamilton Rating Scale for Depression (HAM-D-17) score ≥14; and oncological disease in a non-advanced stage (Karnofsky performance status > 80).

Exclusion criteria will comprise current or prior hospitalization in the next 6 months, planned surgery in the next 6 months, suicidal ideation, substance use, history of significant head trauma, neurological disorders, intellectual deficits, recurrent seizures resulting from head trauma or conditions lowering seizure threshold, concurrent use of medications that increase the risk of epileptic seizures (*e.g.*, antipsychotics, tricyclics, theophylline), glaucoma, retinal detachment, or other serious vision impairments that may prevent the use of virtual reality technology and severe problems with autonomous ambulation.

According to the inclusion/exclusion criteria, recruitment will continue until the target sample size is reached, allowing for randomization and the conduct of interventions (Figs. **1** and **2**).

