#### Sample Size

2.11.1

Sample size and statistical power will be estimated using a Bayesian group sequential design, incorporating an interim assessment at 70% of enrolment [54]. The primary endpoint of the study will be defined as the comparison of remission rates between the TAU and rTMS groups and the TAU *vs*. VR-COG groups.

Literature convincingly supports the efficacy of TMS in major depressive disorder, although not specific to the oncological setting. A recent meta-analysis reported a significant effect on the remission endpoint of rTMS, with an odds ratio of 2.56 (95% CI: 1.73-3.78) [11], corresponding to a risk ratio of 1.5 (95% CI: 1.4-1.6). While no estimate is available on the efficacy of VR-based interventions comparable to VR-COG. Virtual reality-based interventions that do not include cognitive rehabilitation, within oncological settings, have shown effects with a standardized mean difference (SMD) in depressive symptom reduction of -1.11 (95% CI: -3.17 to 0.96) [15]. Considering that traditional (non-VR-based) cognitive rehabilitation for patients with depression, outside of oncology, is associated with a more modest reduction in depressive symptoms (SMD = 0.43; 95% CI: 0.17 to 0.70) [12], a conservative estimate of the effect size would be appropriate. Therefore, an SMD of 0.90, also corresponding to a risk ratio (RR) of 1.5, will be adopted. This design will be explored through a Monte Carlo simulation experiment with 10,000 runs. Each simulation run will assume a scenario with a different combination of effect size and sample size. For each scenario, the proportion of simulated trials correctly identifying at least one effective intervention will be computed, thereby estimating the empirical power of the study in a Bayesian context (Fig. **3**). Specifically, in each run, trial data will be generated under various scenarios assuming a remission rate of 0.6 for the TAU group and a risk ratio (RR) for comparisons with the experimental groups ranging between 1.4 and 1.6 (Fig. **3**). In the simulations, the total sample size n will vary from 50 to 170 patients, with increments of 10 subjects per simulation. The TAU and VR-COG groups will be assigned a sample size twice that of the rTMS group. For example, in a study with 50 participants, 10 patients would be assigned to the rTMS group (available only in Cagliari), 20 to the VR-COG group (Cagliari and Ferrara), and 20 to the TAU group (Cagliari and Ferrara).

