For each Monte Carlo iteration, simulated trial data will be generated assuming a binomial distribution for the TAU group, xTAU ∼ Bin(n1 = 1/5 * n,p1 = 0.6), while for the other groups, the distribution will be xVR-COG ∼ Bin(n = 2/5 * n,p2 = 0.6 * RR). Within each iteration, the posterior probability for the RR will be computed using a beta-binomial distribution with a non-informative prior Beta (1,1). This approach has been chosen to keep the study design conservative during the planning phase. The posterior probability estimates for the RR will be obtained by taking the ratio of the posterior estimates of the remission rates between the two intervention arms (*e.g.*, VR-COG *vs*. TAU and rTMS *vs*. TAU).

Using these posterior estimates of the RR, it will be possible to derive the probability that the RR is greater than 1, applying the efficacy boundary method. This approach would allow for the definition of criteria to declare the intervention effective either at the end of the trial or earlier, at the time of interim analyses. The boundaries will be derived from the cumulative distribution function of a normal distribution, based on the frequentist O’Brien and Fleming boundaries, and translated into a Bayesian framework, as suggested in the literature [55]. The efficacy thresholds will be as follows: φ interim/(z=2.8)=0.997 e φ overall/(z=1.98)=0.976.

An interim analysis is planned at 70% of the total enrolment. If the posterior probability of the intervention’s efficacy exceeds the predefined efficacy boundary at the interim analysis, early termination of that intervention arm for efficacy will be considered. A total sample size of 100 participants (70 at interim analysis, allocated as 14 to rTMS, 28 to TAU, and 28 to VR-COG) would allow for a 41% probability of declaring the intervention effective at interim, assuming a risk ratio of at least 1.5. The evaluation of the other intervention will continue until the completion of the planned enrollment.

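### LOCF, the only missing-data rule, makes anyone without a T1 or later HAM-D-17 score a non-remitter, so unequal loss between arms biases the remission risk ratio

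*Protocol article*

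**What the plan says.** - **Missing-data rule** (Statistical Analysis, 2.11): analysis by intention to treat, with "imputation of missing data according to a Last Observation Carried Forward (LOCF) protocol". The only sensitivity analysis stated there concerns the priors. Methods to Handle Missing Data (2.9.5) describes efforts to keep collecting outcomes after early withdrawal, by remote assessment or new check-ups. It gives no rule for data that are still missing.
- **Primary endpoint** (Sample Size, 2.11.1): the "comparison of remission rates between the TAU and rTMS groups and the TAU" versus VR-COG groups. Neither a HAM-D-17 cut-off for remission nor the visit at which it is judged is printed.
- **Entry** (Participants and Recruitment, 2.2): "depression without psychotic symptoms according to Hamilton Rating Scale for Depression (HAM-D-17) score ≥14".
- **Visits** (Evaluation Tools and Evaluation Timeline, 2.4): HAM-D-17 is taken at "T0 (0 months-baseline), T1 (3 months-post-intervention), T2 (3 months after T1), and T3 (6 months after T1"), with nothing between T0 and T1.
- **Dropout**: it is one of the primary feasibility measures ("Drop-out rates, the proportion of recruited participants among those considered eligible", 2.4). No rate is assumed in the sample size.
- **Operating characteristics** (2.11.1): 81% probability of identifying at least one effective intervention and false positives below 5%, simulated from complete binomial data.

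**The concern.** For a participant lost before T1 the only score to carry forward is the one that showed depression at entry, so LOCF records non-remission without any outcome having been seen. The remission rate in each arm then mixes treatment effect with retention. Retention may well differ by arm. Each experimental arm adds 24 sessions to TAU, participants are unblinded, and Study Limitations (section 4) lists time commitment, discomfort and unfamiliar technology as barriers to participation. Heavier loss in the experimental arms would hide an effect, and heavier loss on TAU would create one. The stated power and false-positive rate allow for neither.

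Two further consequences follow. LOCF treats filled-in values as observed, so posterior intervals overstate precision. The cost-effectiveness ratio uses the T0 to T3 change in quality of life, and LOCF sets that change to zero for anyone lost before T1.

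**Working it through.** **Inputs from the protocol.** TAU remission 0.6 and RR 1.5; Beta(1,1) priors; looks at 70 and 100 patients; 28 TAU, 28 VR-COG and 14 rTMS at interim, so 40/40/20 at the end; boundaries 0.997 and 0.976 for the posterior probability that RR exceeds 1.

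**Assumed.** Dropout before T1 of 10% to 30% per arm, with no later score obtained. Unless stated otherwise, dropout is unrelated to outcome.

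**Step 1: the plan's own figures, complete data.** Simulating the two-look rule with no effect gives 4.7% false positives for at least one arm, in agreement with the stated below 5%. Power for at least one arm is about 94% if both arms have RR 1.5, 89% if only VR-COG does and 72% if only rTMS does. The stated 81% was not reproduced. That is a separate matter, and nothing below depends on it.

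**Step 2: what LOCF does to the rates.** Let p be an arm's true remission rate, d its loss before T1, and r the true remission rate among those lost.

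- LOCF rate = p − d × r
- If loss is unrelated to outcome, r = p, and the LOCF rate = p × (1 − d)
- Apparent RR = true RR × (1 − d_exp) / (1 − d_TAU)

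**Step 3: true RR 1.5 in both arms (p = 0.6 and 0.9).**

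| Dropout TAU / exp. | LOCF rates | Apparent RR | Power, LOCF | Power, observed cases |
|---|---|---|---|---|
| 0 / 0 | 0.60 v 0.90 | 1.50 | 94% | 94% |
| 15% / 15% | 0.51 v 0.765 | 1.50 | 76% | about 88% |
| 10% / 25% | 0.54 v 0.675 | 1.25 | 33% | about 87% |

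The fair comparator for LOCF is the observed-case column, because any method loses some power when data are missing.

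**Step 4: no true effect (p = 0.6 in all arms).**

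| Dropout TAU / exp. | LOCF rates | Apparent RR | False positives, at least one arm |
|---|---|---|---|
| 0 / 0 | 0.60 v 0.60 | 1.00 | 4.7% |
| 15% / 10% | 0.51 v 0.54 | 1.06 | about 8.6% (8.5% to 8.7% across runs) |
| 20% / 10% | 0.48 v 0.54 | 1.125 | about 14% |
| 25% / 10% | 0.45 v 0.54 | 1.20 | about 21% |
| 10% / 25% | 0.54 v 0.45 | 0.83 | about 0.8% |

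**Step 5: varying remission among those lost.**

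No true effect, dropout 30% TAU v 10% experimental:
- r = 0.6: (0.6 − 0.1 × 0.6) / (0.6 − 0.3 × 0.6) = 0.54 / 0.42 = 1.29; false positives 28% to 29%.
- r = 0.3: (0.6 − 0.1 × 0.3) / (0.6 − 0.3 × 0.3) = 0.57 / 0.51 = 1.12; about 14%.
- r = 0: RR 1.00; about 5%.

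True RR 1.5 in both arms, dropout 10% TAU v 30% experimental, with r in the experimental arms 1.5 times that on TAU:
- r = 0.6 on TAU: 0.63 / 0.54 = 1.17; power about 20%.
- r = 0.3 on TAU: (0.9 − 0.3 × 0.45) / (0.6 − 0.1 × 0.3) = 0.765 / 0.57 = 1.34; about 56%.
- r = 0: RR 1.50; about 94%.

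**The case against.** **Direction.** The protocol's features mainly suggest burden, hence more dropout in the experimental arms. In that direction LOCF is conservative: with no true effect, false positives fall to about 0.8%. This stands. A reader might infer that LOCF is expected to manufacture a positive result. The protocol does not support that, because inflation needs higher loss on TAU, which is possible in an unblinded trial but which nothing in the document predicts.

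**Comparator.** Setting 33% against 94% charges LOCF with power that any method would partly lose. This also stands, and the comparison to use is with about 87%. The 94% further assumes that both arms work, whereas the stated 81% is for RR 1.5 in at least one comparison.

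**Stopping treatment is not the same as a missing score.** Section 2.9.5 plans to obtain outcomes after withdrawal, so a reader should not equate leaving the sessions with a missing HAM-D-17. The concern covers only those for whom these efforts fail.

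**Certainty.** Non-remission by rule needs a cut-off below 14 and needs the baseline score to count as a carried observation. Neither is printed, although a score that qualifies as depression at entry could hardly count as remission. It is also not true that every dropout becomes a non-remitter. If remission is judged at T2 or T3, someone lost after T1 keeps the last observed state, and if it is judged at T1, later loss does not touch the endpoint.

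**Legitimacy.** Counting losses as non-remission is a recognised strategy for a binary endpoint and is right if none of those lost would have remitted. It belongs in the plan as a declared sensitivity analysis. Here it arises as a by-product of LOCF and is the only analysis stated.

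**Conclusion.** The concern holds in this form. LOCF is the only missing-data rule stated, and it classifies participants with no post-baseline HAM-D-17 as non-remitters under any cut-off below 14. The RR is biased when such losses differ by arm and some of those lost would have remitted. Equal, uninformative loss leaves the RR unbiased and costs power only (about 76% against 88% using observed cases at 15% dropout).

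The consequence that best fits the protocol's own features is a diluted effect: apparent RR 1.25 for a true 1.5, and power of about 33% against 87%, at 10% v 25% dropout. Inflation of false positives to between about 8.6% and 21% is the mirror case. It requires TAU dropout to exceed experimental dropout by 5 to 15 percentage points, and it shrinks as remission among those lost falls. All these sizes rest on assumed dropout rates and on loss unrelated to outcome, so they show sensitivity and are not forecasts. The change should be made, but the design does not depend on it.

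**What to change.** Replace LOCF with multiple imputation, or Bayesian posterior draws, under missing-at-random, using arm, site and all observed HAM-D-17 scores. Derive remission in each completed data set, analyse it with the planned beta-binomial model and priors, and combine the posteriors. This keeps the remission model and the elicited priors. Replacing the primary model with a longitudinal HAM-D-17 model would cost more, because the priors and the design simulations are built on remission probabilities.

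Add two sensitivity analyses: missing counted as non-remission, and arm-specific departures from missing-at-random. Use the same approach for the secondary and quality-of-life outcomes, including the T0 to T3 gain in the cost-effectiveness ratio. State that the 81% and below-5% figures assume complete data.

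The cost is a revised paragraph and modest extra programming. No new data are needed.
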